### Surgical technique

The hepaticojejunostomy will be performed as a part of pancreatoduodenectomy and can be placed on the same jejunal loop as the pancreatojejunostomy or on a second jejunal loop.

The common preparation before suturing the hepaticojunostomy includes an opening of the hepatic duct with corner sutures and an antimesenterical jejunal incision. After the corner sutures are placed at the hepatic duct, the diameter of the ductus hepaticus is measured in mm and documented in the CRF.

The further procedure depends on the randomized technique:Interrupted suture technique: with this technique both the posterior and the anterior walls are performed single-rowed using interrupted stitches.Continuous suture technique: with this technique both the posterior and the anterior walls are performed single-rowed using continuous sutures.

There are no specifications for the suture material and the number of sutures used, but these data will be documented in the CRF. If an anastomotic leakage is detected intraoperatively, any number of interrupted sutures may be added to the hepaticojejunostomy. The measurement of the duration of the hepaticojeunostomy begins with the first suture (excluding the corner sutures of the hepatic duct) and ends with the cutting of the last thread, which is necessary to complete the hepaticojeunostomy. The application of an abdominal drainage near the hepaticojejunostomy is standard in our department and is recommended, but not mandatory.

Used suture material, number of sutures, number of interrupted stiches, number and place of abdominal drains, and the time for hepaticojejunostomy are documented in the CRF. In addition, the surgeon’s experience performing hepaticojejunostomies is recorded and documented in the CRF.

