### Randomization and blinding

After the inclusion criteria have been confirmed and the patient's consent has been obtained preoperatively by trained medical staff as well as exclusion criteria (e.g., no performance of a hepaticojejunostomy due to irresectability of the pancreatic tumor) have been excluded intraoperatively, randomization will be carried out intraoperatively immediately before the hepaticojejunostomy is performed. Randomization only takes place if the surgeon considers the present situs to be suitable for both suturing techniques and the ductus hepaticus is at least 5 mm (Fig. 1).

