#### Sequence generation

The randomization is designed with fixed block sizes in a 1:1 allocation ratio and is generated using research randomizer (www.randomizer.org). The generation of randomization codes and the randomization on the day of the surgery is performed independently of the surgical team by authorized study personnel only. More details of the randomization will be kept safe and confidential as long as this trial is ongoing.

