The screening form contains demographic data including basis data, disease course, and comorbidities as well as preoperative blood results (including hemoglobin, white blood cells, creatinine, albumin, serum c-reactive protein, and liver enzymes). In the surgical form data about the operation like duration and kind of surgery as well as data about the hepaticojejunostomy (duration, suture material, information about the hepatic duct) is recorded. The postoperative forms include always the documentation of morbidity and mortality as well as at POD 1 and 3 laboratory results (including hemoglobin, white blood cells, creatinine, albumin, serum c-reactive protein, Quick, bilirubin as well as liver enzymes and cholestasis parameters) and the bilirubin concentration in the abdominal drain being close to the hepaticojejunostomy. At discharge histological results and length of hospital stay are additionally documented.

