### Statistical considerations and sample size calculation

Literature was systematically reviewed to identify all published data to this topic (see Supplementary Fig. 1). There were no randomized controlled trials and only one retrospective analysis from Japan, which compared the interrupted suture technique with the continuous suture technique in the setting of liver transplantations [11]. However, these data are not suitable for a meaningful sample size calculation, as the leakage rates of this reported trial come from a different setting and seem to be high compared to data derived mainly from hepaticojejunostomies only or as part of a pancreatoduodenectomy (5.6% using interrupted sutures [1] and 2.3% using both techniques [2], respectively).

Therefore, an adaptive sequential sample size design was chosen: The sample size per patient group was set exploratively at a group size of 50 patients. Total sample size was 100 patients. The prevalence of the primary endpoint in the 100 patients examined then forms the data basis for an adequate further sample size analysis and consequently for a sample size adjustment. To proceed the study with the then new calculated sample size, some criteria have to be met: First, the absolute difference in the primary endpoint must be at least 1% to justify clinical relevance of the study. Second, the calculated sample size per group should not exceed 1000 patients in order to be able to meaningfully end the study.

Due to the design with multiple testing an error correction will be performed in statistical analysis. Due to the lack of reliable data in the literature, this adaptive design offers the best opportunity to get meaningful data with adequate power.

Statistical analysis will be performed using SPSS software. An intention-to-treat and a per-protocol-analysis will be used for the analysis of the primary outcome. Comparisons of metric and ordinal data will be calculated with the Student *t*-test or Mann-Whitney *U* test. The chi-square test was used for categorical data. Statistical significance will be set at *p* < 0.05.

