## Discussion

This clinical trial is one of the first randomized controlled study to investigate the safety and efficiency of two commonly applied suture techniques (the interrupted versus the continuous suture technique) in patients undergoing a hepaticojejunostomy during pancreatoduodenectomy. In addition to this study, there could be identified a second ongoing registered study on the same issue in China (ChiCTR1900020605).

Although the performance of a hepaticojejunostomy is a common procedure in hepato-pancreato-biliary surgery and a leakage of this anastomosis is associated with relevant morbidity and mortality, very few studies have dealt with this topic to date. A comparison of the suturing techniques with regard to the leakage rates was only carried out in one retrospective study in the setting of liver transplantations. This illustrates the necessity and usefulness of a study to compare the suturing techniques for hepaticojejunostomy during pancreatoduodenectomy.

Before initiating the present trial, a Germany-wide survey was carried out on the application of the various suturing techniques for hepaticojejunostomies. This confirmed that there is enormous heterogeneity in the technology used. While the majority use both techniques depending on the intraoperative situs, 40% of those questioned are rigidly attached to their technique. The bile duct diameter was cited as the most important decision criterion for those who use both techniques. This shows that very small bile ducts in particular can often be better treated using the interrupted suture technique. Therefore, the lower limit of the bile duct diameter in our study was set to 5 mm.

Due to the small amount of data comparing surgical techniques for hepaticojejunostomies, the sample size calculation is a particular challenge. There are only data available comparing the interrupted and the continuous suture technique in the liver transplant setting, where the risk of leakage is likely to be higher. Published data from the pancreatic surgery setting show lower leakage rates. However, in this pancreatic setting, there are no comparative data. To compensate for this lack of data, an adaptive design with an interim analysis after 100 patients was incorporated. At this point in time, the sample size can be adjusted, which significantly increases the accuracy of the sample size calculation.

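### The metric secondary endpoints get unadjusted two-sample tests although likely covariates are already recorded; adjusted models could give more precision for little cost

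*Protocol article*

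**What the plan says.** The statistics section (Statistical considerations and sample size calculation) assigns one class of test to each data type. For metric and ordinal data: "Comparisons of metric and ordinal data will be calculated with the Student" t-test or the Mann-Whitney U test. For categorical data: "The chi-square test was used for categorical data". It mentions no covariates.

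The metric secondary endpoints, listed under Aim of the study and study endpoints, include total operative time, duration of the hepaticojejunostomy and the postoperative rise in γGT, alkaline phosphatase and bilirubin.

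Three candidate covariates are collected:
- Duct diameter. Under Surgical technique, "the diameter of the ductus hepaticus is measured in mm and documented in the CRF". It is known before allocation, because a minimum of 5 mm is a condition for it: "Randomization only takes place if the surgeon considers the present situs to be suitable for both suturing techniques and the ductus hepaticus is at least" that size.
- Surgeon experience. In the same section, "the surgeon’s experience performing hepaticojejunostomies is recorded and documented in the CRF".
- Preoperative bloods. The screening form holds "preoperative blood results (including hemoglobin, white blood cells, creatinine, albumin, serum c-reactive protein, and liver enzymes".

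On allocation, the section on sequence generation says: "The randomization is designed with fixed block sizes in a 1:1 allocation ratio". It adds that further details stay confidential while the trial runs.

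**The concern.** The first stage has 50 patients per group, and leakage rates of 2.3% to 5.6% are cited. That means 2.3 to 5.6 expected leaks among 100 patients, so the first stage says little about the primary endpoint. If the two continuation criteria are not met, the trial goes no further than this stage. The time and laboratory endpoints would then be its most informative comparisons.

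For those endpoints the patient mix matters. It is plausible that duct size and the surgeon's routine affect suturing time, and that the preoperative value predicts the postoperative value of a cholestasis parameter. If so, an unadjusted test leaves explainable variation in the error term. The confidence interval is then wider than it need be, although the data to narrow it are largely collected already.

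**Working it through.** **No figure to reproduce.** The 50 per group was set exploratively, not derived from a power formula. The calculation below takes that size as given.

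**Inputs.** From the article: n = 50 per group and a significance level of 0.05. Assumed: a two-sided test (sidedness is not stated), an effect of 0.5 SD, and a multiple correlation ρ of 0.2 to 0.5 between covariates and outcome. The article gives no value for either of the last two.

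**Time endpoints.** Adjustment multiplies the residual variance by 1 − ρ². With the normal approximation,

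power = Φ( 0.5 / [√(2/50) × √(1 − ρ²)] − 1.96 ), where √(2/50) = 0.2.

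| ρ | 1 − ρ² | 2.5/√(1 − ρ²) | Power | Equivalent n per group, 50/(1 − ρ²) |
|---|---|---|---|---|
| 0 (unadjusted) | 1.00 | 2.50 | 71% | 50 |
| 0.2 | 0.96 | 2.55 | 72% | 52 |
| 0.3 | 0.91 | 2.62 | 75% | 55 |
| 0.5 | 0.75 | 2.89 | 82% | 67 |

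The exact t-test gives 69.7% for the unadjusted case, hence about 70%.

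**Cholestasis parameters.** Take equal variance σ² before and after surgery, and correlation r between the two.
- Change score: variance 2σ²(1 − r).
- ANCOVA on the preoperative value: variance σ²(1 − r²).
- Ratio: (1 − r²) / [2(1 − r)] = (1 + r)/2.

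For r = 0.3 the ratio is 0.65, and for r = 0.5 it is 0.75 (r assumed). Defining the endpoint as an increase already uses the baseline, but subtraction uses it less efficiently than ANCOVA whenever r < 1.

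**Is the baseline recorded?** The preoperative list names liver enzymes but not bilirubin. The list for postoperative days 1 and 3 names bilirubin and cholestasis parameters separately. Both lists are introduced as non-exhaustive, so preoperative availability is neither shown nor excluded.

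**Leakage, for comparison.** This was simulated with three covariates (odds ratios per SD 2, 1.5 and 1.5) and true rates of 5.6% and 2.3%.
- 500 per group: power is 78% with chi-square and 78% with adjusted logistic regression.
- 50 per group: there are on average 4 leaks. The adjusted model cannot be estimated in 36% of runs, and its Wald test rejects in 1%, against 11% for chi-square.

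**Validity of the unadjusted test.** With the same covariates present and 4% leakage in both arms, chi-square rejects in 3.7% of runs at 50 per group and 4.3% at 500. The nominal level of 5% is kept.

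**The case against.** The strongest reply is that covariate adjustment of secondary endpoints is ordinary analysis-plan content, and that plan is not shown. Default tests in a condensed article do not exclude adjusted models. This largely stands, and it is why the point is minor. It does not remove the point, because the article does not stay silent: it names the tests for metric data, and a better method than the named one is available.

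A second reply is that prognostic strength is not shown. This stands. The article says of its survey that "The bile duct diameter was cited as the most important decision criterion for those who use both techniques", but that concerns how surgeons choose a technique in routine practice. Technique is randomized here, so the statement is no evidence of prognosis. The leakage risk factors listed in the Background include neither duct diameter nor surgeon experience. The gain can therefore be given only as an assumed range, and at ρ = 0.2 it is about two points of power.

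A reader might infer three stronger points that the document does not support:
- That uncorrected chance imbalance is an error. At 50 per group a given covariate differs by more than 0.25 SD in 21% of trials (0.25/0.2 = 1.25 standard errors). Randomization already allows for this, and the test keeps its level.
- That allocation is unstratified. Further details are withheld, so this is unknown.
- That leakage should be adjusted too. The simulation shows no gain in a large trial, and an unworkable model in the first 100 patients.

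**Conclusion.** The point holds as a minor efficiency improvement for the metric secondary endpoints. The stated tests are valid but may be less precise than the collected data allow. On the assumptions above (two-sided 0.05, 0.5 SD effect, 50 per group), adjustment lifts power from about 70% to between 72% and 82% for ρ of 0.2 to 0.5. For the cholestasis parameters, ANCOVA needs 65% to 75% of the change-score variance for r of 0.3 to 0.5, assuming equal variances before and after surgery. If the covariates are not prognostic, the time endpoints gain nothing and lose almost nothing: with two single-term covariates, residual degrees of freedom fall from 98 to 96. Nothing here affects the primary endpoint.

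**What to change.** In the statistics section, state the following for the metric secondary endpoints:
- Duration of the hepaticojejunostomy and total operative time: a linear model, on the log scale if skewed, with technique, duct diameter in mm and surgeon experience. Add centre once more than one centre recruits (the article reports only one so far), and any stratification factor used in the allocation.
- γGT, alkaline phosphatase and bilirubin: ANCOVA of the postoperative value on the preoperative value, after confirming that each is recorded at screening.
- Leakage: keep the stated unadjusted test.

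The cost is analysis wording and a few model terms to fix in advance, including how experience is coded. Duct diameter, surgeon experience and a centre number are already in the CRF. Only the preoperative cholestasis values, bilirubin above all, need checking.

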### Randomization and blinding

After the inclusion criteria have been confirmed and the patient's consent has been obtained preoperatively by trained medical staff as well as exclusion criteria (e.g., no performance of a hepaticojejunostomy due to irresectability of the pancreatic tumor) have been excluded intraoperatively, randomization will be carried out intraoperatively immediately before the hepaticojejunostomy is performed. Randomization only takes place if the surgeon considers the present situs to be suitable for both suturing techniques and the ductus hepaticus is at least 5 mm (Fig. 1).

#### Sequence generation

The randomization is designed with fixed block sizes in a 1:1 allocation ratio and is generated using research randomizer (www.randomizer.org). The generation of randomization codes and the randomization on the day of the surgery is performed independently of the surgical team by authorized study personnel only. More details of the randomization will be kept safe and confidential as long as this trial is ongoing.

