### Trial design and study setting

The objective of the HEKTIK trial is to investigate whether there is a significant difference in the occurrence of anastomotic leakage between the two groups interrupted suture versus continuous suture technique for performance of a hepaticojejunostomy during pancreatoduodenectomy. The study is designed as a randomized controlled, national (Germany), patient-blinded multicenter trial with the performance of a hepaticojejunostomy in interrupted suture technique in one arm and in continuous suture technique in the other arm. To homogenize patient collective and the risk profile for occurrence of anastomotic leakage of hepaticojejunostomy only patients with pancreatoduodenectomy were included. Until now, there is only the institution of the study coordinators, that recruits patients for the HEKTIK trial. Further high-volume centers are planned to initiate soon.

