#### Allocation concealment mechanism

Ass allocation concealment mechanism, the authorized study personnel, who perform randomization, are not involved in the inclusion of patients as well as in the treatment part.

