#### Blinding

To reduce bias blinding of study contributors is a common and effective measure [10]. However, in our study, only patients were blinded to the study treatment. Surgeons cannot be blinded as they perform the study therapy. The data analyst, data collector, and the outcome assessor were not blinded due to the robust outcome parameters.

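### Fixed block sizes in an open surgical trial, with a surgeon's suitability opinion just before allocation, leave the next allocation partly predictable to a team that shares past allocations

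*Protocol article*

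**What the plan says.** - **Sequence generation:** "The randomization is designed with fixed block sizes in a 1:1 allocation ratio". The size is not given: "More details of the randomization will be kept safe and confidential as long as this trial is ongoing". Codes are generated and patients randomised "performed independently of the surgical team by authorized study personnel only".
- **Allocation concealment mechanism:** the safeguard is separation of staff: "the authorized study personnel, who perform randomization, are not involved in the inclusion of patients", nor in treatment.
- **Blinding:** "only patients were blinded to the study treatment", and "Surgeons cannot be blinded as they perform the study therapy".
- **Randomization and blinding:** allocation happens in theatre, directly before the anastomosis. "Randomization only takes place if the surgeon considers the present situs to be suitable for both suturing techniques", and the duct must measure at least 5 mm.
- **Patient withdrawal criteria:** the surgeon may also keep a patient out if he or she thinks one technique is the only possible or the better one. The reason goes into the screening log.
- **Trial design and study setting:** "Until now, there is only the institution of the study coordinators, that recruits patients for the HEKTIK trial"; more centres are planned.

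**The concern.** The person who makes the last eligibility decision also knows the technique used in every case he or she performs. With fixed blocks, those past allocations carry information about the next one. If a surgeon expects the technique he or she likes less for a given duct, the suitability opinion offers an accepted reason not to randomise that patient. Preferences linked to anatomy are plausible: the Background and Discussion report that 40% of surveyed hospitals always use one technique, and that duct diameter is the main criterion among those using both.

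The arms could then differ in baseline risk. The leakage rates cited under Statistical considerations are 2.3% and 5.6%, or 50 × 0.023 = 1.2 to 50 × 0.056 = 2.8 expected events per arm of 50. Continuation depends on an absolute difference of at least 1%, and the same data set the later sample size. A small distortion could therefore matter.

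**Working it through.** The plan gives no predictability figure to reproduce. The block size is withheld, so a range is assumed.

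**1. Known fixed block of size b = 2m, 1:1, all earlier allocations known in order.**

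Share of allocations that are certain = 1/(m + 1):
- b = 4: 1/3 = 33.3%
- b = 6: 1/4 = 25.0%
- b = 8: 1/5 = 20.0%
- b = 20: 1/11 = 9.1%

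Share guessed correctly by always naming the arm that is behind (a coin toss when level) = 0.5 + (4^m / C(2m, m) − 1) / (2b):
- b = 4: 0.5 + (16/6 − 1)/8 = 70.8%
- b = 6: 0.5 + (64/20 − 1)/12 = 68.3%
- b = 8: 0.5 + (256/70 − 1)/16 = 66.6%
- b = 20: 0.5 + (1,048,576/184,756 − 1)/40 = 61.7%

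Chance alone gives 50%.

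**2. Block size unknown.** Blocks end in balance, so the arm that is behind can be read from the running totals. Simulating sequences of 100 for an observer who tracks only these totals gave 70.8%, 68.0% and 66.2% for blocks of 4, 6 and 8. Above-chance guessing therefore does not need the size. Certainty does.

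**3. Incomplete knowledge of the sequence.** For a block of 4, a surgeon who sees only his or her own cases guesses correctly 53.5% of the time with two surgeons, 52.6% with three and 51.4% with five (simulation, cases assigned to surgeons at random). The figures in steps 1 and 2 thus need pooled, ordered knowledge.

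**4. Randomly varying sizes 4, 6 and 8, equally likely.**
- *Guessing the arm behind:* (4 × 0.708 + 6 × 0.683 + 8 × 0.666)/18 = 68.1%, no better than a fixed block of 6.
- *Certain allocations:* counting only places where the running imbalance has reached its maximum of 4 gives (1/3) × (2/70)/6 = 0.16%, about 0.2%. That count is narrow, because after four of one arm in a row from a level start all four remaining places are certain: 4 × 0.16% = 0.6%. A like-for-like count with step 1 takes an observer who knows the set of sizes and updates on the full sequence. It gave about 2.3% (simulation, 3,000 sequences of 100), against 20–33% for the known fixed blocks. If the set of sizes is also undisclosed, fewer allocations can be inferred with certainty.

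**5. Illustration of possible bias, on assumed figures only.** Assume 30% high-risk patients, leakage of 9.0% in them and 2.28% in the rest (overall 0.3 × 9.0 + 0.7 × 2.28 = 4.3%, inside the cited range), no true difference, and a team that keeps out high-risk patients when it predicts the disfavoured arm. Keeping out 25%, 50% or 100% of them gives a spurious difference of 0.1, 0.4 or 0.8 percentage points for blocks of 4, and 0.1, 0.3 or 0.7 for blocks of 6.

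**The case against.** The case against has several good parts.

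- *Who sees the sequence.* A reader might infer that the recruiting team sees every earlier allocation. The documents do not say so. Each surgeon knows his or her own cases, and the surgeon's experience is recorded case by case (Surgical technique), which suggests that operators vary. This stands: the 67–71% figures are conditional on a team that shares allocations.
- *Block size.* It is deliberately withheld, and the plural wording does not establish one constant size. This stands for the certain share. It does not help against guessing the arm that is behind.
- *Safeguards.* Independent staff and confidentiality protect the list itself, and the log makes exclusions visible afterwards. They do not prevent inference from operations already performed, and a log entry that one technique was better would look legitimate whether or not it was influenced by a prediction.
- *Irreparable bias.* A reader might infer that no analysis could correct such selection. That is too strong: duct diameter is documented for each patient and exclusions are logged with reasons, so steering on recorded features can be examined and partly adjusted for. Unrecorded features would remain.
- *Single centre.* This is the present state of a trial planned as multicentre, not a fixed feature.
- *Centre lists.* Stratification by centre may be among the withheld details, so its absence from the article proves nothing.

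**Conclusion.** The point holds as a design vulnerability. The article states fixed rather than varying blocks, surgeons know what they performed, and a subjective decision stands directly before allocation. For a team that pools its allocations, the next arm can be guessed about 67–71% of the time for blocks of 4 to 8. If the block size also becomes known, 20–33% of allocations are certain. For a surgeon limited to his or her own cases the gain over chance is only about 1 to 3 percentage points (block of 4, two to five surgeons).

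Nothing in the document shows that steering took place, and the bias of 0.1 to 0.8 points in the illustration rests wholly on assumed risk groups and behaviour. Nor would varying the block sizes bring guessing to 50%: it removes nearly all certainty, not all predictability. The change is worth making because it is cheap and recruitment is still open.

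**What to change.** For all patients not yet randomised, and for every new centre, replace the fixed blocks with randomly varying block sizes, one list per centre, with neither the sizes nor their range disclosed to sites. Preferably include some larger blocks: a mix of 4, 6 and 8 leaves guessing near 68%, while a block of 20 brings it to about 62%.

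Add a time stamp to the existing screening-log entry, so that the surgeon's suitability decision and its reason are final before the allocation is requested. The log and the recording of reasons are already in the protocol; only the time stamp and the order of steps are new.

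Cost: one new list per centre and one extra log field. Downside: a possible imbalance of a few patients at the 100-patient look. Within a centre, an unfinished block can leave the arms apart by at most half its size (4 for a block of 8, 10 for a block of 20). Patients already randomised are unaffected.

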## Background

Hepaticojejunostomies represent a common step during pancreatic and liver surgery including partial pancreatoduodenectomy, major liver resections, and bile duct resections. Overall, a hepaticojejunostomy is considered as a safe procedure with low rates of postoperative complications including a leakage rate of 2.3% to 5.6% [1, 2]. However, failure of this anastomosis leads to considerable consequences with a high risk of prolonged hospitalization and the need for interventional drainage or re-laparotomy, which is associated with high morbidity and mortality, even in high volume centers [3, 4]. Known risk factors for leakage are previous chemoradiation, preoperative biliary drainage, impaired liver synthesis capacity, malnutrition, obesity, and anastomosis at the level of hepatic duct bifurcation [1].

However, leakage of a hepaticojejunostomy could always be associated with the surgical technique used. There are especially two common techniques used for hepaticojejunostomy: the interrupted suture technique and the continuous suture technique. According to a current national survey in Germany 56% of the participating hospitals stated that they use both techniques for performing a hepaticojejunostomy depending on the surgical sites, while 40% of the hospitals adhere always to one of the mentioned two techniques. These results show a relevant heterogeneity of the techniques used among hospitals in Germany [5]. There is an ongoing debate between advocates of both techniques, who argue with universal use (also for small ducts) and a potentially lower stenosis rate for the interrupted suture technique and with a better sealing of the anastomosis and operative time saving for the continuous suture technique.

Despite the frequent necessity of hepaticojejunostomies in surgery and the relevant consequences for the patient with leakage, there are no randomized studies to compare the different surgical techniques. For this reason, the presented randomized controlled multicenter trial was initiated to assess whether there is a significant difference in the occurrence of anastomotic leakage between the two groups interrupted suture versus continuous suture technique for performance of a hepaticojejunostomy during pancreatoduodenectomy.

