### Documentation and data management

The collected data is documented using a case report form (CRF) with pseudonymization of patients. For data protection, the CRF contains only an individual identification code including a center number and a patient number. All CRFs are reviewed by the investigators. All data collected is treated with strict confidentiality in accordance with the data protection and the GCP guidelines. Access to the data is only permitted to authorized personnel.

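### The stated tests pool all patients and ignore centre, although further centres are planned: valid, but wasteful for time and cost endpoints if several centres contribute

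*Protocol article*

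**What the plan says.** - **Design.** Under Trial design and study setting: "The study is designed as a randomized controlled, national (Germany), patient-blinded multicenter trial". At publication "there is only the institution of the study coordinators, that recruits patients for the HEKTIK trial", but "Further high-volume centers are planned to initiate soon".
- **Allocation.** Under Sequence generation: "The randomization is designed with fixed block sizes in a 1:1 allocation ratio". No stratification factor is named. The same section adds: "More details of the randomization will be kept safe and confidential as long as this trial is ongoing".
- **Tests.** Under Statistical considerations and sample size calculation: "Comparisons of metric and ordinal data will be calculated with the Student" t-test or the Mann-Whitney U test, with chi-square for categorical data and significance at p < 0.05. None of these uses centre.
- **Size.** The same section sets 50 patients per group for the first stage and allows a recalculated size of up to 1000 per group.
- **Endpoints and technique.** Total operative time, duration of the anastomosis and its material costs are secondary endpoints. The Surgical technique section leaves suture material and number of sutures free.
- **Data.** Under Documentation and data management: "the CRF contains only an individual identification code including a center number and a patient number".

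**The concern.** The analysis section names its tests, and they are pooled tests that do not fit the multicentre design described a few sections earlier. Free choice of suture material and number makes it plausible that anastomosis time and material cost will differ between hospitals. Where they do, the pooled comparison leaves those differences in the residual variance. Time and cost are endpoints that 50 patients per group could realistically inform, so the lost precision falls where the first stage has most to offer. Centre is already recorded, so nothing needs to be collected to avoid the loss.

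**Working it through.** **No figure of the plan to reproduce.** The first-stage size, 2 × 50 = 100, was set exploratively. The protocol gives no effect size, SD, ICC or power for any metric endpoint.

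**Inputs from the protocol.** 50 patients per arm; 1:1 allocation in fixed blocks; significance at 0.05.

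**Assumptions, not in the protocol.** Two-sided testing; ICC (share of an endpoint's variance explained by centre) of 0.1, 0.2 or 0.3; five centres; blocks of four.

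**Step 1: detectable difference at 80% power.**
- Centre ignored: (1.96 + 0.84) × √(2/50) = 0.56 SD.
- Centre in the model: the residual variance is multiplied by (1 − ICC), so the detectable difference is 0.56 × √(1 − ICC) = 0.53, 0.50 and 0.47 SD for ICC 0.1, 0.2 and 0.3.

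**Step 2: simulation, 100 patients in five equal centres.** The t-test is compared with a linear model containing arm and centre. The power columns use a common list and a true difference of 0.56 SD. The last column uses centre-wise lists and no true difference.

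| ICC | Power, pooled | Power, centre in model | True size of pooled test, centre-wise lists |
|---|---|---|---|
| 0.1 | 79% | 81% | 4.1% |
| 0.2 | 80% | 85% | 3.6% |
| 0.3 | 82% | 91% | 2.4% |

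Repeat simulations moved the sizes by up to about half a percentage point and left the pattern unchanged. The large-sample formula 2 × (1 − Φ(1.96/√(1 − ICC))) gives 3.9%, 2.8% and 1.9%. It exaggerates the conservatism with only five centres, so the simulated sizes are the ones to use.

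**Step 3: validity.** On a common list the pooled t-test rejected a true null in 4.7% to 5.6% of runs for ICC 0 to 0.3, and its mean standard error matched the actual spread of the estimate. With centre-wise lists the standard error was too large: at ICC 0.3 it averaged 0.193 against a true 0.167. That error is in the conservative direction.

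**Step 4: one dominant centre.** With centre sizes 80/5/5/5/5, ICC 0.2 and a 0.5 SD difference, power was 75.9% pooled against 76.6% with centre on a common list, and 75.2% against 78.1% on centre-wise lists. With one centre there is no centre term and no gain.

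**Step 5: leakage.** At the rates cited in the protocol, 100 patients yield about 2 to 6 leaks (2.3% and 5.6% of 100). Stratifying so few events by centre gains next to nothing.

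**Step 6: technique effect that varies by centre.** With an assumed SD of 0.3 for the effect across centres, ICC 0.2 and a zero average effect, the pooled t-test rejected in 10.0% (common list) and 7.9% (centre-wise lists) of runs. With a plain centre term the rates were 10.9% and 11.2%. The centre term does not cure this problem.

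**The case against.** **The article is condensed and an analysis plan may add centre.** This is the strongest objection. It would succeed if the article were silent on the tests. It is not: it names them, and all are pooled. An unseen plan may already adjust for centre, in which case the fix reduces to bringing the two texts into line.

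**Only one centre was recruiting, and the trial calls itself explorative.** This stands as a limit on size. The number of further centres is not given and five is an assumption.

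Four stronger readings are tempting, and the documents do not support them:

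- *The randomisation is not stratified by centre.* The article names no factor but expressly withholds further details, so this is not established.
- *The pooled tests give misleading significance.* On a common list they hold their level, because chance centre imbalance is already part of their standard error. On centre-wise lists they err on the cautious side.
- *The national survey shows that centre matters for these endpoints.* That "40% of the hospitals adhere always to one of the mentioned two techniques" describes preference among German hospitals, not time, cost or leakage in trial centres. Since technique is randomised, local habit would act mainly by making the technique effect differ between centres, which a centre term does not repair (Step 6).
- *An enlarged trial needs protection from chance centre imbalance in leakage.* Such imbalance shrinks with size. For a centre supplying one fifth of patients, the SD of the between-arm difference in its share is √(0.2 × 0.8 × 2/50) = 8 percentage points at 50 per arm and √(0.2 × 0.8 × 2/1000) = 1.8 points at 1000 per arm.

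**Conclusion.** The point holds as a matter of efficiency, not validity. The protocol fixes pooled tests for a trial that it calls multicentre and plans to extend, while the centre identifier lies unused in the data. If several centres of similar size contribute and centre explains 10% to 30% of the variance in time or cost, leaving centre out forgoes about 2 to 9 points of power on a common list. On centre-wise lists it turns a nominal 5% test into one of roughly 4.1% to 2.4%. If the coordinating centre supplies about 80 of 100 patients, the gain is about 0 to 3 points; if it remains the only centre, it is nil. These sizes rest on an assumed ICC and five assumed centres. The quantified effect is on secondary endpoints, and the primary endpoint at 100 patients is essentially unaffected.

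**What to change.** In Statistical considerations and sample size calculation, state that once a second centre contributes patients:

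- metric endpoints are analysed with a linear model containing arm and centre, on the log scale for skewed times and costs, or with a van Elteren test stratified by centre;
- binary endpoints, including leakage, are analysed with a Mantel-Haenszel method stratified by centre;
- centres below a pre-stated size are pooled;
- the present pooled tests are kept as sensitivity analyses.

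In Sequence generation, state whether lists are separate by centre and, if they are not, use one list per centre from the next opening onward. This can be said without disclosing block sizes.

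The cost is a few lines of text and one list per centre, with no extra patients or data. With a single centre the linear model reduces to the present t-test, apart from any log scale. The downside is that very small centres must be pooled. The wording should be fixed before further centres contribute data, because the Blinding section says the analyst is not blinded and a later choice would look data-driven.
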